### Study measures

#### Primary outcomes

The primary study outcomes will be derived from the variables coded (Table 4) using recorded conversations that parents and teens had when engaging in the simulator and naturalistic drives.

Once reliable, study team members will code whether parents identify the hazard, whether the parent verbally identifies roadway hazards, if hazard identification uses a hazard anticipation communication (i.e., higher-order communication), if instruction precedes or follows the hazard event, if the hazard anticipation communication includes elements of motivational interviewing, and how many times parents provide functional driving instructions. Hazard anticipation communication, a form of higher-order driving instruction that can be applied more generally to driving (e.g., “When there are brake lights ahead, you should be ready to brake too.”), will be coded when parents indicate why the hazard is dangerous by causally connecting dangerous features and their potential outcomes. Functional instruction will be coded for instruction that applies only to the current context (e.g., “Slow down.”). We will also code whether the teen verbally identifies the hazard via hazard anticipation communication or by only pointing out the hazard and if identification precedes or follows the hazard event. Measures will be captured for each hazard that is presented in the simulator drive for a total of 17 repeated measures per dyad. For each of the 17 scenarios embedded in the simulator drive, a binary indicator reflecting presence or absence will coded for hazard anticipation communication, its sub codes, and hazard identification only. The number of functional driving instructions produced by the parent per hazard scenario will be recorded as a count.

Unlike simulator drives, hazards encountered in during naturalistic driving are not standardized. Therefore, coding will focus on general hazard anticipation patterns rather than per-hazard responses. Raw counts of each conversational measure will be recorded. because drives varied in length (10–30 min), counts will be modeled as a rate per 10 min of drive time. Each dyad contributed four naturalistic drives.

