##### Primary analysis

The primary set of analyses will examine the impact of the intervention on real-time parental instruction surrounding hazard identification and mitigation separately for the simulator and naturalistic drives.

**Simulator drives** Generalized linear mixed models will be used to predict conversational measures using a fixed effect of condition and covariates detailed above. For presence/absence measures (e.g., hazard anticipation communication), the probability of occurrence will be modeled using a mixed-effects logistic regression modeling approach. Condition will be included as a fixed effect, along with relevant demographic and driving covariates. Potential random effects of participant and hazard scenario will be determined using loglikelihood ratio testing. Outcomes will be interpreted as probability of occurrence. For count measures (e.g., functional driving instruction), the frequency of occurrence will be modeled using a mixed-effects position regression approach. Again, condition will be included as a fixed effect, along with relevant demographic and driving covariates and random effects structure determined with loglikelihood testing. Outcomes will be interpreted as incident rate ratios. Additionally, we will examine the distributions of teen temperament, family communication pattern, and parenting style and explore if intervention differences are suggested. P-value adjustments for multiple tests will be undertaken. We predicted that parents in the intervention arm of the study will exhibit increased probability and incidence of higher-order instruction of hazard anticipation and response with their teen.

**Naturalistic drives** The rate for each conversational outcome per 10 min of naturalistic driving will be modeled using a mixed-effects Poisson regression. The log of drive duration in 10-minute units will be included as an offset term to account for variation in drive length, such that model coefficients reflect expected counts per 10-miunte interval, rather than per drive. As with simulated driving, condition will be included as a fixed effect along with demographic and driving covariates. A random intercept of dyad will also be included to account for the correlation among the repeated drives within dyad. Drive number (1–4) will also be explored as a potential covariate to account for potential change over the naturalistic driving period.

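### Minor: the naturalistic-drive Poisson model has no term for extra variation between a dyad's drives, so the exploratory drive-number term may get too small a standard error

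*Protocol article*

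**What the plan says.** The Protocol article, Primary analysis, Naturalistic drives, fixes the model family: "The rate for each conversational outcome per 10 min of naturalistic driving will be modeled using a mixed-effects Poisson regression". Length is handled by an offset: "The log of drive duration in 10-minute units will be included as an offset term to account for variation in drive length". The effect under test enters as usual: "condition will be included as a fixed effect along with demographic and driving covariates". The random part is one term: "A random intercept of dyad will also be included to account for the correlation among the repeated drives within dyad". Time enters only tentatively: "Drive number (1–4) will also be explored as a potential covariate to account for potential change over the naturalistic driving period".

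Under Primary outcomes, the article states "Each dyad contributed four naturalistic drives" and gives the range of lengths: "because drives varied in length (10–30 min), counts will be modeled as a rate per 10 min of drive time". The same section says that hazards met on these drives are not standardised, unlike the 17 scripted simulator scenarios. Table 4 lists five measures coded as counts on the naturalistic drives.

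For the simulator drives, the random-effects structure is left to likelihood-ratio testing. For the naturalistic drives it is stated outright. No drive-level term, dispersion parameter or robust standard error is named.

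**The concern.** Conditional on the dyad and the covariates, a Poisson model sets the variance of a drive's count equal to its mean. The dyad intercept allows some parents to instruct more than others. It does not allow one parent to instruct more on one drive than another beyond chance and length. These are parents' usual lessons, and the article does not control what is met on the road, so some excess variation between a dyad's drives is to be expected.

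The term exposed to this is drive number, the article's only term for change over the recording period. If its standard error is too small, the analyst may keep the covariate wrongly, or describe a rise or fall in instruction over the four drives that is noise. The planned p-value adjustments deal with the number of tests and do not correct a standard error that is too small.

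**Working it through.** The article gives no count rates or variances, so it has no figure of its own to reproduce on this point.

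**Inputs from the article.** 102 completing dyads (Study population); equal allocation within sex blocks (Randomization), taken as 51 per arm; four drives per dyad of 10–30 min; log-duration offset; dyad random intercept.

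**Assumed.** Rates of 0.5 to 10 per 10 min; dyad log-SD 0.5 (0.1 as a sensitivity check); extra drive-level log-SD σ of 0, 0.3 and 0.5; durations uniform on 10–30 min; drive number linear; Wald tests at two-sided 5%.

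**Step 1: where the information on drive number lies.** Write the count of dyad i on drive j as Poisson with mean t_ij · exp(x_i'β + γj + b_i), where t_ij is duration and b_i the dyad intercept. Given the dyad's total, the split over its four drives is multinomial with probabilities t_ij·exp(γj) / Σ_k t_ik·exp(γk). Condition and b_i cancel. The split carries essentially all the information on γ, the model fixes its variance, and the dyad variance cannot enlarge it.

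**Step 2: size of the excess.** With an extra drive-level term of log-SD σ, the variance-to-mean ratio given the dyad is 1 + μ(exp(σ²) − 1), where μ is the expected count. For a 20-minute drive, μ = 2 × rate.
- Rate 2, σ = 0.5: 1 + 4 × 0.284 = 2.14.
- Rate 10, σ = 0.3: 1 + 20 × 0.0942 = 2.88.

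If dyads are alike, the model SE should be about 1/√ratio of the true SD. At rate 2, σ = 0.5 this is 1/√2.14 = 0.68. Simulation with dyad log-SD 0.1 gives 0.71. With dyad log-SD 0.5 it falls to about 0.6, because high-count dyads weigh most and are the most overdispersed.

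**Step 3: simulation of the stated model.** Maximum likelihood with adaptive quadrature, both true effects zero, dyad log-SD 0.5, 400 runs per row. The Monte Carlo SE at 5% is √(0.05 × 0.95/400), about 1.1 points.

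| Rate per 10 min | σ | Variance/mean | Drive number: false positives | Drive number: model SE / empirical SD | Condition: false positives |
|---|---|---|---|---|---|
| 0.5 | 0 | 1.00 | 6.2% | 0.97 | 6.2% |
| 0.5 | 0.3 | 1.09 | 6.0% | 0.90 | 4.8% |
| 0.5 | 0.5 | 1.28 | 8.8% | 0.85 | 6.5% |
| 2 | 0 | 1.00 | 2.2% | 1.06 | 3.8% |
| 2 | 0.3 | 1.38 | 12.2% | 0.76 | 5.2% |
| 2 | 0.5 | 2.14 | 27.0% | 0.58 | 6.0% |
| 5 | 0 | 1.00 | 4.5% | 1.00 | 4.5% |
| 5 | 0.3 | 1.94 | 20.2% | 0.66 | 5.0% |
| 5 | 0.5 | 3.84 | 38.5% | 0.44 | 6.5% |
| 10 | 0 | 1.00 | 4.0% | 1.05 | 5.0% |
| 10 | 0.3 | 2.88 | 30.8% | 0.51 | 5.5% |
| 10 | 0.5 | 6.68 | 52.0% | 0.33 | 5.8% |

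Separate runs (600 per setting) at two other rates, for σ = 0, 0.3 and 0.5, give 4%, 11% and 16% at 1 per 10 min, and 5%, 27% and 46% at 8 per 10 min. The two columns for drive number agree: an SE ratio of 0.33 implies 2[1 − Φ(1.96 × 0.33)] = 52%.

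**Step 4: the condition effect.** Condition varies only between dyads. Extra drive-level noise adds to the spread of dyad totals, and the fitted dyad variance takes it up. Over all settings run, including dyad log-SD 0.1 and σ = 0.7, the condition test rejects in 3.8–7.2% of runs, with model SE / empirical SD of 0.96–1.04.

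**Step 5: remedies.** A negative binomial model with the same dyad intercept (300 runs, 8 per 10 min) gives 6–7% for drive number and 4–5% for condition. Dyad-robust standard errors on the Poisson fits give 4.5–6.2% for drive number in eight of nine settings and 9.8% in the ninth, with SE ratios of 0.95–1.04. At rate 2, σ = 0.5, the model-based rate of 24.5% in that run falls to 5.8%.

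**The case against.** Every stated hypothesis concerns condition, and the condition test is sound under the stated model. Drive number is a candidate covariate that may never enter the model, and no hypothesis about a time trend is attached to it. Keeping it wrongly would not bias the condition contrast either, since each dyad supplies four drives and drive number is balanced across arms by design. The sizes above rest on assumed rates and SDs, and for rare codes the inflation is slight. A dispersion check could also sit in an analysis plan that is not shown.

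All of this limits the weight of the point, and it is why the point is minor. It does not remove it. The article does more than omit a detail: it names the distribution and the random term, and that model cannot carry the excess variation that uncontrolled road conditions make plausible.

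A reader might infer that drive-to-drive variation is ignored altogether. It is not: the model carries Poisson variation, drive length and, if kept, drive number. A reader might also extend the point to the simulator counts or to a condition-by-drive term. The article plans no such interaction. It treats hazard scenario as a candidate random effect with no fixed scenario term, and it names no Poisson model for risky driving events.

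**Conclusion.** The point holds as a minor one, for the naturalistic counts only. If a dyad's drives vary beyond Poisson noise and length, the standard error of the exploratory drive-number term is too small. At assumed drive-level log-SDs of 0.3 to 0.5, false positives run from about 6–16% at 0.5–1 per 10 min to about 27–52% at 8–10 per 10 min. Frequent codes are the most exposed. With no extra variation the error is nominal. The direction follows from the likelihood; the size depends on rates and variances that the article does not give.

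The stronger reading, that the primary comparison of conditions on these drives is invalid, is not supported: that test stays close to 5% in every setting tried.

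**What to change.** In Primary analysis, Naturalistic drives, replace the Poisson model with a mixed-effects negative binomial model that has the same offset and dyad intercept. Alternatively, keep Poisson and add a drive-level random intercept, or use dyad-robust standard errors. State that any drive-number estimate, and any decision to keep that covariate, comes from this model.

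The cost is one extra dispersion parameter (none with robust errors) and wider intervals for drive number. The condition result should barely move. Coding and analysis are still described in the future tense, so the change can be made before the data are analysed.

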##### Secondary analysis

The secondary set of analyses will examine any changes to teen’s driving behavior in response to parental instruction during the simulator drive. More specifically, we will use mixed-effects models to predict outcomes of risky driving behaviors and lane changes. Each model will include a fixed effect of condition and covariates detailed above. Potential random effects of participant and hazard scenario will be determined using loglikelihood ratio testing. P-value adjustments for multiple tests will be undertaken. We expected that teens of parents in the intervention arm of the study will exhibit improved driving responses to potential hazards in the simulator drive.

#### Sample size

Power calculations based on the medium to large effect sizes reported in previous studies of parent-focused intervention to improve teen driving^15,16^ indicated that a minimum of 100 dyads (*N =* 200 participants total) would be needed to detect medium-size effects at a 0.80 level of power. Power calculations were conducted in G*Power [23].

### Ethics

This study received ethical approval from the Institutional Review Board at the University of lowa [202010535]. Several measures were taken to ensure that individuals were not coerced into participation. First, during the recruitment processes, messages were added to all emails exclusively stating that individuals were not required to reply to emails and could choose to opt out from receiving them at any time. Second, during the consent process, participants were told that being involved in the study was completely voluntary and they could stop at any time. Participants were assured they would not lose any benefits to which they were otherwise owed had they chosen to cease participation in the study at any point. Participants were also encouraged to ask any clarifying questions during the consent process. Participant confidentiality was ensured during the consent process and maintained throughout the entire study timeline. Steps were taken to maintain participant confidentiality and compliance with all relevant rules and regulations: (1) all participant information (names, dates of birth, phone numbers, addresses) was kept on a digital master list that only the study team could access; (2) participant dyads were all assigned anonymous IDs that were used in place of their names on all study materials; (3) during the consent process, participants were informed of the risks and confidentiality concerns of being involved in research and were provided with details of storing and sharing their video and performance data. Participants were given the choice to consent to storing their data in central repositories sponsored by the National Institutes of Health or other federal agencies and sharing it with other qualified researchers. Participants were assured that their data would not be shared with anyone outside of the study team if they did not consent to it.

### Dissemination

We will use a variety of common methods to disseminate our study findings. These methods will include traditional academic outlets (e.g., peer reviewed journals, conference presentations, incorporation of findings into course content where appropriate) and key stakeholders (e.g., Iowa Department of Transportation, area driver educators, Teen Safe Driving Coalition, National Foundation for Teen Safe Driving). We will also disseminate our findings to study participants using lay language and infographics to aid comprehension. We will also work closely with University of lowa and Injury Prevention Research Center communication experts, who will disseminate our research findings to audiences via news and other outlets to ensure our findings have the greatest impact possible.

## Discussion

The Hazard Anticipation Program for Parents (HazAPP) was developed to improve teens’ hazard anticipation skills by providing parents with the needed tools to provide real-time hazard anticipation instruction to their teen in the learner phase of licensure. The current RCT seeks to evaluate the feasibility of a web-based program, HazAPP, and determine its ability to shift parents from reactive, functional instruction toward proactive hazard anticipation communication.

HazAPP is an innovative approach to improving teens’ hazard anticipation skill because it goes beyond existing systems of teen driver education to specifically train parents to teach teens in hazard anticipation – the leading cause of teen motor-vehicle crashes [5, 24, 25]. HazAPP also fills an important gap in teen crash prevention because there are currently no programs available for supporting parent instruction of roadway hazards. Additionally, HazAPP’s web-based design is highly accessible, making the program ideal for all families, including those who may lack access to other driving resources.

The current study design has several limitations. First, the sample size was determined using only medium-to-large effects sizes, making the detection of smaller, yet meaningful differences more challenging. However, repeated observations (i.e., simulated hazards) and planned analysis were both chosen to improve estimates. Second, the sample was recruited largely via convenience sampling in the University area. While efforts to broaden our recruitment pool using Facebook were beneficial for overall generalizability, more testing is needed to determine true generalizability. Third, teens were not given direct access to HazAPP, as the intention was to deliver the program to parents who are supervising teen driving. Future work should evaluate the impact direct access may have on subsequent teen driving performance. Fourth, while information regarding family communication patterns and parenting style were included, these may not adequately capture the quality of the parent-teen relationship. Fifth, the study captures a brief portion of the supervised driving period and does not quantify changes to teens’ independent driving behaviors or safety outcomes. Finally, while the study achieved an even sex balance and sex will be included as a covariate in all planned analyses, the current sample was not powered to detect sex-moderated intervention effects. Given that male teens face substantially greater crash risk, we will conduct exploratory analyses examining sex as a potential moderator of intervention effects. However, as these analyses were not preregistered, findings should be interpreted with appropriate caution and replicated in future work.

If effective, HazAPP will improve parental instruction when teaching teens to identify and respond to potential roadway hazards during the learner phase of licensure and may have important implications for crash prevention among novice teen drivers. Assuming our hypotheses are correct, next steps include conducting an efficacy trial with a longer follow-up period to better examine the impact of the intervention over the learner period of licensure. Additionally, future work should examine the impact of HazAPP on teens’ crash risk upon beginning to drive independently.

## Data Availability

The datasets used and/or analyzed during the current study are available from the corresponding author on reasonable request.

## Abbreviations

HazAPP: The Hazard Anticipation Program for Parents
NIH: National Institutes of Health
IRB: Institutional Review Board
RCT: Randomized Control Trial
